#### Warm-up exercise

Warm-up exercise is based on *Baduanjin* combined with lip-constricted breathing and abdominal breathing. *Baduanjin* is a traditional Chinese physical exercise that involves mild exercise and respiratory regulation [19].

#### Aerobic exercise

Considering the tolerance of patients with COPD, sports coaches integrate aerobic exercise into a set of aerobics. Aerobics include eight movements and could be performed in the standing or sitting position according to the patient’s condition. Each movement is performed in 4–6 sets of 8–16 repetitions. Between each set, there is a break of 10 s. If the patient is unable to tolerate the exercise, the break time could be extended.

#### Resistance training

Resistance training could also be performed while standing or sitting. The sports coach integrates resistance exercises into a set of aerobics, including eight movements with a stretch belt (1.5 m, 22 pounds). Each movement consists of 4–6 sets of 8–16 repetitions. Between each set, there is a break for 10 s. If the patient is unable to keep up, the break time will be extended.

#### Respiratory muscle training

Patients receive respiratory muscle training through abdominal breathing, wherein the abdomen gently puffed-up during inhalation and sank during exhalation. A sandbag weighing 5 kg will be placed on the abdomen, followed by abdominal breathing for 3 min.

#### Respiratory rhythm adjustment

Patients breath is through the nose and breath out through the mouth slowly. Respiratory rhythm adjustment runs through the training.

In both groups, each patient has an exercise log, which is completed by a supervisor who instructed the sessions online. The exercise log contains adverse events, completed exercises, and a record of vital signs before and after exercise.

### Outcome measures and follow-up

Data on the outcomes will be collected at baseline and after 12 weeks. Patients are followed up weekly in the outpatient department or through online methods, including telephone and WeChat. The primary outcome measure is exercise tolerance using the 6-MWT. Secondary outcomes are the peak oxygen uptake (V̇O_2_) of cardiopulmonary exercise tests, the COPD Assessment Test (CAT), and the St. Georges Respiratory Questionnaire (SGRQ). Other outcomes include changes in postbronchodilator forced expiratory volume at 1^st^ second (FEV1), forced vital capacity (FVC), body fat and muscle composition, mental status measured using the Hamilton rating scale for depression scores (HAMD-24) and the Hamilton Anxiety rating scale (HAMA).

The investigator will inquire about the occurrence of adverse events. The details of every adverse event will be reported in the case report form (CRF). The same investigator will record all outcome measures to maintain standardization in the procedure.

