## Methods and analysis

### Study setting

This study is a prospective, parallel-group randomized, controlled, exploratory clinical trial. Participants will be recruited from the Guangdong Provincial Hospital of Chinese Medicine Clinic. They are outpatients attending a clinic or inpatients being discharged home and evaluated by two experienced respiratory physicians. Patients are invited to meet with the research physicians to discuss any remaining questions and sign the informed consent. Thereafter, the participants are randomly assigned to either the trial or control group as a ratio of 1:1. The trial group will receive PR integrated with coached exercise training. The control group will receive a traditional PR program. Owing to the exercise intervention, it is not possible to blind participants or those involved in the provision of care. However, the researchers collecting primary data and performing statistical analyses will be blinded to the allocation. The design is open label with only outcome assessors and data analysts being blinded, so unblinding will not occur. The study design is shown in Fig. 1.

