### Adverse event reporting

Adverse events will be recorded in CRF (Case Report Form). Serious adverse events will be reported within 24 h to the principal investigation and Institutional Review Board. The steering committee consists of a pulmonologist and a respiratory nurse who will survey the study procedure and evaluate serious adverse events. The steering group is the trialists of this study. If there is any damage related to the study, the research group will pay the medical expenses and make corresponding financial compensation according to laws and regulations.

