### Data management and statistical analysis

Researchers will make appointments for the next follow-up to promote participant retention. Data will be collected in the CRF on paper by the same investigator. All the CRF on paper will be stored in a locked cabinet. Access to the data sets is only available to the investigators in this study. Incomplete data of patients who are lost to follow-up for various reasons will be eliminated. Ethics Committee of Guangdong Provincial Hospital of Chinese Medicine makes a visit per year and checks the presence and completeness of the investigation file. All substantial amendments will be notified to the Committee, and non-substantial amendments will be recorded.

Outcome measures will be analyzed using a *t*-test at the end of the trial. IBM SPSS statistical software for Windows (Version 23.0) is used to analyze the data for the outcome measures. Data is presented as the mean and standard deviation.

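### The investigator who asks unblinded patients about adverse events also appears to record every outcome, which puts the claimed assessor blinding at risk

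*Protocol article*

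**What the plan says.** Study setting accepts that "it is not possible to blind participants or those involved in the provision of care". It then claims one protection: "the researchers collecting primary data and performing statistical analyses will be blinded to the allocation". It adds: "The design is open label with only outcome assessors and data analysts being blinded, so unblinding will not occur".

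Outcome measures and follow-up assigns the duties. "The investigator will inquire about the occurrence of adverse events"; the details go into the CRF; and then "The same investigator will record all outcome measures to maintain standardization in the procedure". The same section describes contact during treatment: "Patients are followed up weekly in the outpatient department or through online methods, including telephone and WeChat".

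Data management and statistical analysis states: "Data will be collected in the CRF on paper by the same investigator". Adverse event reporting confirms that adverse events belong in that form. Table 1 schedules adverse event reporting during weeks 1–12 and again at week 13, when the final outcomes are measured.

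The exercise log is separate. Under Respiratory rhythm adjustment, the supervisor who instructs the sessions completes it in both groups, and it holds adverse events, completed exercises and vital signs.

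**The concern.** Patients know their allocation, and the programmes are easy to tell apart. The trial group does coached aerobics, stretch-belt resistance work and abdominal breathing under a 5 kg sandbag. The control group mostly walks and swims. Recording the details of an adverse event often means asking what the patient was doing at the time, and the answer can identify the arm. If the person who asks also records the outcomes, the assessor may know the allocation before the final assessment.

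The primary outcome depends on effort and is performed under encouragement. The Hamilton depression and anxiety scales are to be recorded by the same person. Because patients and providers are unblinded, assessor blinding is the only blinding the design claims at the point of measurement. The article describes no measure to preserve it while adverse events are being asked about.

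**Working it through.** **Roles side by side**

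| Duty | Who, according to the article | Section |
|---|---|---|
| Collect primary data | Researchers blinded to allocation | Study setting |
| Ask about adverse events | The investigator | Outcome measures and follow-up |
| Record all outcome measures | The same investigator | Outcome measures and follow-up |
| Collect data in the paper CRF, which includes adverse events | The same investigator | Data management and statistical analysis; Adverse event reporting |
| Complete the exercise log, including adverse events | The session supervisor | Respiratory rhythm adjustment |

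1. Under Outcome measures and follow-up, the sentence naming the same investigator closely follows the one on adverse event enquiry, in the same short paragraph. The natural antecedent is the person just named.
2. The section on data management uses the same phrase for the CRF, and the CRF holds the adverse events.
3. Table 1 places adverse event reporting before and at the final assessment. If the enquiry discloses the programme, it can do so before the last 6MWT and Hamilton ratings.
4. No section separates the two duties, restricts the assessor's access to the log, or asks patients not to mention their programme.

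**The plan's own figure.** Inputs from Sample size calculation: difference 25 m, SD 44.6 m, power 80%, significance level 0.05. Sidedness is not stated; two-sided is assumed.

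n per group = 2 × [SD × (z₀.₉₇₅ + z₀.₈₀) / difference]² = 2 × [44.6 × (1.960 + 0.842) / 25]² = 49.96, rounded up to 50.

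This reproduces the stated 50 per group. The exact t-test gives 51, and a one-sided test would give about 40 to 41, so the plan's figure is two-sided.

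**Illustration of what a shift would do.** The document gives no size for assessor bias, so the shift b below is assumed. With no true effect and 50 per group:

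- Standard error = 44.6 × √(2/50) = 44.6 × 0.2 = 8.92 m.
- Two-sided rejection rate = 1 − Φ(1.960 − b/8.92) + Φ(−1.960 − b/8.92).

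| Assumed shift b | Share of 25 m | b / 8.92 | Rejection rate |
|---|---|---|---|
| 0 m | 0% | 0 | 5.0% |
| 5 m | 20% | 0.56 | 8.7% |
| 10 m | 40% | 1.12 | 20.2% |
| 15 m | 60% | 1.68 | 39.1% |

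The noncentral t distribution gives 8.6% at 5 m and 19.9% at 10 m, which is the same to the nearest whole percent. These figures would apply to a shift from any source. They show how sensitive the test is and are not evidence that this role assignment produces a shift.

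**The case against.** A reader might infer that the article contradicts itself, that the blind is certain to be broken, or that the 6MWT will be biased. The text supports none of these, and the case against them is strong:

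- A single recorder for all outcomes is a standardization measure and is compatible with that person being blinded. Nothing says this investigator knows the allocation, delivers training or makes the weekly contacts.
- The phrase about the same investigator could mean one recorder across patients and visits, rather than the person who asks about adverse events.
- Recording is not necessarily measuring. Spirometry, for example, is performed by a technician, and no section says the recorder conducts the walk test.
- Both groups exercise, so an adverse event question need not disclose the programme.
- Encouragement in the 6MWT is standardized, and keeping the better of two walks is a fixed rule for both groups. The COPD Assessment Test and the St. George's questionnaire are completed by patients; spirometry and body composition are instrument readings.
- The statement that unblinding will not occur may mean only that an open-label design needs no code-break procedure.

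These points stand as limits on the conclusion. They do not remove it. If the phrase means only one recorder across visits, the text still leaves open whether that person also asks about adverse events. Standardized wording limits differential encouragement but does not exclude differences in delivery, and it has no bearing on the Hamilton ratings. An article may leave operational blinding procedures to the full protocol, but this one itself assigns the roles, and on its natural reading it assigns them in a way that weakens its own blinding claim.

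**Conclusion.** The concern holds as a risk. On the natural reading, one investigator asks unblinded patients about adverse events, records all outcomes and completes the CRF, so the assessor blinding claimed under Study setting cannot be relied on as the roles are written. It is not shown to be lost.

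This rests on two assumptions: that the same investigator is the person making the adverse event enquiry, and that some patients' answers would disclose their programme. The 6MWT is partly protected by standardized encouragement; the Hamilton ratings have no comparable safeguard in the text. The size of any bias cannot be estimated, and the figures of about 9% and 20% depend entirely on the assumed 5 m and 10 m shifts. The change is still worth making, because it is cheap and protects the only blinding the design claims.

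**What to change.** In Outcome measures and follow-up and in Data management and statistical analysis, state that:

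- adverse events and weekly vital signs during follow-up are collected by the session supervisor, who already records them in the exercise log, on a separate section of the CRF;
- the outcome assessor sees patients only at baseline and at the end-of-study visit, and has no access to the log or the adverse event pages;
- the assessor asks patients not to mention their exercise programme;
- at the final visit, all outcome testing is completed before any adverse event enquiry.

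In Study setting, reword the clause on unblinding so that it says only that no code-break procedure is needed.

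The cost is protocol wording and a split CRF. No extra staff are needed, because the supervisor already records this information. The trade-off is that adverse events are then collected by an unblinded person; that already happens in the log, but the article should say so.

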### Measurements

#### 6-min walking test

This test measures the distance a participant can walk in 6 min. The patients will be instructed to walk as far as possible in 6 min and receive recommended standardized encouragement. Two tests will be performed on each occasion, and the best distance is recorded. A 30-min rest will be mandatory between the first and second 6-MWT [20, 21].

#### Peak oxygen uptake of cardiopulmonary exercise tests

Cardiopulmonary exercise testing (CPET) will start with an initial rest of 3 min, followed by unloaded cycling for 3 min and a subsequent increment of 5–15 W after each minute. The aim is achieving a total exercise performance time of 8 to 12 min. Patients are asked to maintain a pedaling frequency of 50–60 rpm on a cycle ergometer (SCHILLER CS-200 Ergo- Spiro, Switzerland). If the patients display symptoms such as unsustainable dyspnea or leg fatigue, chest pain, ECG-significant ST-segment depression, and a drop in systolic blood pressure or oxygen saturation (SpO_2_) ≤ 84%, the test will be stopped. V̇O_2_ will be recorded as the mean value of VO_2_ during the last 20 s of the test. VO_2_ will be expressed both as an absolute value (l/min) and in terms of mL/kg/min [22, 23].

#### COPD Assessment Test (CAT)

CAT is a patient completes an 8-item questionnaire that assesses the impact of COPD on self-reported health status and symptoms [24]. Each item is scored from 0 to 5 points (0 indicating no impact or symptoms and 5 indicating the worst possible impact or symptoms) summing up to a total CAT score in the range of 0–40 points.

#### St. Georges Respiratory Questionnaire

The SGRQ is a self-administered questionnaire designed to measure self-perceived impairments in health and quality of life in individuals with airway diseases [25]. The three component scores of the questionnaire, including symptoms, activity, and impact (on daily life) were calculated, giving a total score between 0 and 100, wherein 0 indicates good health and 100 indicates very poor health.

#### Pulmonary function testing

Pulmonary function tests are performed by spirometry using the same machine and the same technician for all patients according to international recommendations [26, 27]. A flow-sensing spirometer and a body plethysmograph connected to a computer (Master Screen Diffusion Combined Pulmonary Function Tester, Jaeger, Germany) will be used for the measurements.

#### Body fat and muscle composition

Body fat and muscle composition will be measured using multifrequency bioelectrical impedance analysis (BIA) via a body composition analyzer (InBody 770, Biospace Co Ltd, Seoul, South Korea). The participant stands barefoot on the platform of the device with the soles of their feet on the electrodes. The participants then grasp the handles of the unit with their thumb and fingers to maintain direct contact with the electrodes and stood still for 1 min while maintaining their elbows at full extension and shoulder joints abducted to approximately 30° angle. During the assessment, BIA analyzers introduce a small electrical current into the body and measure the resistance or impedance to the current flow to calculate skeletal muscle, fat content, and other components of the body. Data on total body composition, body fat percentage, muscle mass, and bone mass will also be collected.

#### Hamilton Rating Scale for Depression (HAMD-24) and Hamilton Anxiety rating (HAMA) scales

HAMD-24 and HAMA are used to evaluate depression and anxiety levels of participants [28]. The HAMD scale includes 24 problem items, which can be classified into seven-factor structures: anxiety/somatization, body mass, cognitive impairment, day-night change, block, sleep disturbance, and sense of hopelessness. A total score of ≥ 8 indicates that the patient has positive depressive symptoms. The HAMA scale contains 14 items, most of which can be scored on a 0–4 scale.

### Participant timeline

The study will last for 3 years. Recruitment of patients started in March 2021. Baseline information including sex, age, body mass index, and history of smoking will be collected at the beginning. Vital signs including blood pressure, heart rate, oxygen saturation, and respiratory rate are collected every week during the period of intervention to evaluate safety. Outcome data are collected before intervention and at 12 weeks. The protocol follows the Standard Protocol Items: Recommendations for Interventional Trials (SPIRIT) 2013 [29]. And A brief SPIRIT flow diagram is shown in Table 1. A populated SPIRIT checklist is provided in Additional file.

**Table 1 Tab1:** Tabulated summary of the study schedule

Timepoint	Baseline (t0)	Week 1–12 (t1)	Week 13 (t2)
Enrollment:			
Eligibility screen	** × **		
Informed consent	** × **		
Demographics	** × **		
Medical history	** × **		
Interventions:			
Trial group		** × **	
Control group		** × **	
Assessment:			
6-MWT	** × **		** × **
V̇O_2_ of CET	** × **		** × **
CAT	** × **		** × **
SGRQ	** × **		** × **
Pulmonary function testing	** × **		** × **
Body fat and muscle composition	** × **		** × **
HAMD-24	** × **		** × **
HAMA	** × **		** × **
Safety monitoring:			
Vital signs	** × **	×	** × **
Adverse event reporting		** × **	** × **

### Adverse event reporting

Adverse events will be recorded in CRF (Case Report Form). Serious adverse events will be reported within 24 h to the principal investigation and Institutional Review Board. The steering committee consists of a pulmonologist and a respiratory nurse who will survey the study procedure and evaluate serious adverse events. The steering group is the trialists of this study. If there is any damage related to the study, the research group will pay the medical expenses and make corresponding financial compensation according to laws and regulations.

### Data management and statistical analysis

Researchers will make appointments for the next follow-up to promote participant retention. Data will be collected in the CRF on paper by the same investigator. All the CRF on paper will be stored in a locked cabinet. Access to the data sets is only available to the investigators in this study. Incomplete data of patients who are lost to follow-up for various reasons will be eliminated. Ethics Committee of Guangdong Provincial Hospital of Chinese Medicine makes a visit per year and checks the presence and completeness of the investigation file. All substantial amendments will be notified to the Committee, and non-substantial amendments will be recorded.

Outcome measures will be analyzed using a *t*-test at the end of the trial. IBM SPSS statistical software for Windows (Version 23.0) is used to analyze the data for the outcome measures. Data is presented as the mean and standard deviation.

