## Abstract

**Background:**

Chronic obstructive pulmonary disease (COPD) is the most common chronic lung disease creating an immense burden on social health care systems. Pulmonary rehabilitation (PR) has proven to be effective in patients with COPD. However, exercise training as the basis of PR becomes extremely tedious, occasionally causing a loss of perseverance in patients. Therefore, we considered an approach that makes this technique interesting and easier to persist. The aim of this project was to explore an exercise training approach based on PR-integrated coached exercise training to promote the new exercise training approach as a form of group rehabilitation activity in the future.

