### Eligibility criteria

We will include participants aged between 40 and 80 years, diagnosed with COPD (a post-bronchodilator FEV1 < 70% and < 80% of predicted normal values), who are clinically stable, have not experienced an acute exacerbation for at least 4 weeks before the trial, do not participate in systematic exercise training in the past 6 months, and have a 6-min walk test (6MWT) distance between 350 and 550 m.

We will exclude participants with severe comorbidities, including coronary heart disease, arterial aneurysm, severe hepatic and renal dysfunction, and uncontrolled hypertension. Patients with mental diseases, deafness, limb activity disorder, and inability to cooperate are also excluded from the trial.

Patients can leave the study at any time for any reason. Intervention can also be ended by the investigators if the patient is uncooperative and does not attend study visits. This study will be ended in case of any abundance in adverse events or procedure-related complications.

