### Sample size calculation

For the primary outcome, a change of 25 m in the 6-MWT distance is considered to be the minimal important difference (MID) in patients with COPD [16], based on a two-sample independent *t*-test with a given MID of 25 m, standard deviation of 44.6 m, power of 80%, and significance level of 0.05 [17]. Accordingly, the calculated sample size of each group is 50. Assuming a dropout rate of 15% resulted in 18 patients being included in the final study population.

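### Eliminating the data of patients lost to follow-up makes the primary 6MWT comparison a complete-case analysis, with a risk of attrition bias of unknown direction

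*Protocol article*

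**What the plan says.** Under Data management and statistical analysis, the protocol article states: "Incomplete data of patients who are lost to follow-up for various reasons will be eliminated". The same section gives the test: "Outcome measures will be analyzed using a *t*-test at the end of the trial".

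Under Outcome measures and follow-up, "The primary outcome measure is exercise tolerance using the 6-MWT", and "Data on the outcomes will be collected at baseline and after 12 weeks". Table 1 shows the same two assessments, with the second placed at week 13. No intermediate 6MWT is scheduled.

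The sample size section plans on "a given MID of 25 m, standard deviation of 44.6 m, power of 80%, and significance level of 0.05" and allows for 15% dropout.

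Three other places bear on who may be lost:
- Study setting says that participants and care providers cannot be blinded, while those who collect the primary data and analyse them are.
- The abstract motivates the trial by saying that "exercise training as the basis of PR becomes extremely tedious, occasionally causing a loss of perseverance in patients". The Discussion adds that the new programme should be easier to adhere to, and Interventions says that exercise training is the only difference between the arms.
- Eligibility criteria says: "Intervention can also be ended by the investigators if the patient is uncooperative and does not attend study visits".

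**The concern.** The elimination sentence is a stated rule, not a detail left open for a statistical analysis plan. It applies whatever the reason for loss. Because there is no 6MWT between baseline and the end, a patient lost in between contributes nothing to the primary comparison.

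Randomisation protects the comparison of all patients as assigned. It does not protect a comparison of those who happen to have a final value. If the exercise programme affects who stays in follow-up, and if those who leave would have walked a different distance from those who stay, the complete-case difference is not the effect of assignment. The trial's rationale makes both conditions plausible: it expects the arms to differ in how easy the training is to sustain, and sustained training is expected to affect walking distance. Blinded outcome assessment does not help, since it protects the measurement and not the selection of who is measured. Recruiting extra patients to cover dropout protects power but leaves the bias untouched.

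**Working it through.** **Inputs from the protocol article.** MID 25 m, SD 44.6 m, power 80%, significance level 0.05 (taken as two-sided), 15% dropout, 1:1 allocation.

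**The plan's own sample size.** n per group = 2 × [44.6 × (1.960 + 0.842) / 25]² = 49.96, rounded up to 50. This reproduces the article: "the calculated sample size of each group is 50". An exact t-test calculation gives 50.94, that is 51.

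**Dropout allowance.** 50 / (1 − 0.15) = 58.8, so 59 per group and 118 in total. The total of 118 is derived here. The article prints 18, which does not follow from its inputs and is a separate error. If 118 are enrolled, 59 × 0.85 = 50.15 per group remain and power stays near 80%. The rule is therefore a question of bias, not of power.

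**Bias formula.** In one arm, let d be the share lost and g the mean 6MWT result of completers minus the mean that the lost patients would have had. The mean of all randomised patients is (1 − d) × completer mean + d × lost mean = completer mean − d × g. Hence

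bias in the difference (trial minus control) = d_T × g_T − d_C × g_C.

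The formula holds for final distance or for change, provided g is defined on the same scale.

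**Assumed values.** The documents give neither g nor the loss by arm. For g, the range runs from 25 m (the MID) to 44.6 m (the planning SD). The unequal splits are chosen to average the planned 15%.

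| Loss trial / control | Gap | Bias | Share of 25 m MID |
|---|---|---|---|
| any | 0 m in both arms | 0 m | 0% |
| 15% / 15% | equal in both arms | 0 m | 0% |
| 10% / 20% | 25 m in both arms | 25 × (0.10 − 0.20) = −2.5 m | 10% |
| 10% / 20% | 44.6 m in both arms | 44.6 × (−0.10) = −4.46 m | 18% |
| 5% / 25% | 25 m in both arms | 25 × (−0.20) = −5.0 m | 20% |
| 5% / 25% | 44.6 m in both arms | 44.6 × (−0.20) = −8.92 m | 36% |
| 15% / 15% | 44.6 m in trial arm only | 0.15 × 44.6 = +6.69 m | 27% |

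Swapping the loss rates reverses the sign of the unequal-loss rows. So does assuming that the lost patients would have done better than the completers.

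**Effect on the test.** In the last row, SE = 44.6 × √(2 / 50.15) = 8.91 m and bias / SE = 0.75. If there is no true difference, the chance of a significant result is about 0.12 instead of 0.05. So equal loss in the two arms does not by itself guarantee safety.

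**The case against.** Several counter-arguments have force.

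**Patients who stop exercising are not expressly removed.** A reader might infer that the rule restricts the analysis to those who persevered. The text does not say that. It removes incomplete data of patients lost to follow-up, and someone who stops training but attends the final visit has complete data. This stands: the point concerns patients without a final 6MWT.

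**The investigator rule is narrower than it may look.** A reader might infer that investigators can drop uncooperative patients from the analysis. The Eligibility criteria sentence also requires that the patient does not attend study visits, and it ends the intervention, not follow-up or use of the data. Nor does it say which investigators decide, so an unblinded decision is an inference. What remains is that the article does not say that follow-up continues afterwards.

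**The rationale is about exercise, not attendance.** The abstract says that perseverance is lost occasionally, and the deletion rule speaks of various reasons for loss. Arm-related loss is plausible but not shown. Adherence is the motivation and not a listed outcome, so it would be wrong to say that the rule removes a declared endpoint.

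**Retention measures exist.** Follow-up is weekly, in clinic or by telephone or WeChat, and appointments are made to promote retention. These may reduce loss, but the plan still allows for 15%.

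**The trial calls itself exploratory, and the article is a condensed text.** Missing wording on intention to treat, imputation or sensitivity analysis may stand in a fuller document and is not held against it. The deletion sentence is different, because it is stated. An analysis plan that kept every randomised patient would contradict it.

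**Conclusion.** The concern holds in this form: the article fixes a complete-case rule for the primary comparison, which carries a plausible risk of attrition bias of unknown size and direction. It does not follow that the estimate is biased, or that any bias would favour the coached programme. If the control arm loses more patients who would have walked less far, the rule understates the benefit of coaching. The bias is zero if loss is unrelated to outcome, or if both the loss and the gap are equal in the two arms.

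In the illustrations with the same gap in both arms, the shift is 2.5 to 8.9 m in either direction, or 10% to 36% of the effect the trial is sized to detect. These figures rest on assumed gaps of 25 to 44.6 m and assumed loss splits averaging 15%, none of which the documents supply. The rule should still be replaced: it governs the single primary comparison, and a final 6MWT that was never sought cannot be recovered later.

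**What to change.** Replace the elimination sentence with a statement that:

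- all randomised patients are analysed in the group to which they were assigned;
- the final assessment already in the schedule is sought from every patient, whether or not the exercise programme is continued;
- ending the intervention does not end follow-up, and all data collected are kept;
- missing final 6MWT values are handled by a pre-stated method that uses data already collected, for example multiple imputation from arm, baseline 6MWT and sessions recorded in the exercise log;
- a sensitivity analysis covers values missing not at random, for example by shifting the imputed values by a range of amounts in each arm.

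Keep the complete-case t-test as a secondary analysis, and report loss by arm with reasons. Multiple imputation is one reasonable choice and not the only one. With no intermediate 6MWT, its gain depends on how well the exercise log predicts the final distance, which is untested here. That makes seeking the final visit from everyone the more valuable part.

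The cost is a little more follow-up effort for patients who stop, at a visit already planned, and somewhat more analysis. The estimate may move in either direction.
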